#### Evaluation of dentin sensitivity—primary outcome

3.1.12

Before removal of the carious dentin, Group 1 and Group 2 volunteers will respond to the Visual Analogue Scale (VAS),^[38]^ which will obey the following protocol: gauze isolation of neighboring teeth; light air jet in the tooth with MIH for 2 seconds; sensitivity evaluation through the VAS scale. This sequence will be repeated at the end of the procedure, after insertion of the glass ionomer cement.

#### Microbiological evaluation

3.1.13

Prior to the removal, the soft dentine of each selected tooth will be collected. The removed tissue will be standardized using a No. 2 Meyhoefer curette and will be deposited in a test tube containing 3.8 mL of Transport Medium-Phosphate Buffered Saline (PBS, Labcenter, São Paulo). The biological material will be deposited in the transport flask containing glass beads by shaking the tube at maximum speed in a Vortex apparatus for homogenization of the biological material for 30 seconds. After stoving at 37°C for 30 minutes to liquefy the gelatin from the medium, the dental biofilm will be dispersed into the transport flask containing glass beads by shaking the tube shaker at full speed for 30 seconds.

Subsequently, biological material will be serially diluted in the order of 10^1^ to 10^6^ in peptone water and inoculated into culture media in Petri dishes. Aliquots of dilutions 10^4^, 10^5^, and 10^6^ will be seeded on the surface of Brucella Agar (Difco, Kansas City, USA) plus sheep defibrinated blood (50 mL/L), hemin (Inlab, São Paulo, Brazil) (5 mg/mL), and menadione (Inlab) (10 mg/mL) for the determination of the total viable microorganisms. Aliquots of dilutions 10^3^ and 10^4^ will be seeded in MitisSalivarius agar medium (Difco) to determine the total number of streptococci (S). Biofilm aliquots without dilution and at dilutions 10^1^ and 10^2^ will be seeded in MitisSalivarius Agar medium plus debacitracin to determine the streptococci mutans (SM) population.^[39]^ 100 μL aliquots of each dilution will be seeded on the agar surface and spread with the aid of a Drigalski loop.

In order to verify the presence of lactobacilli (LB), aliquots (100 μL) without dilution and in the dilution 10^2^ will be inoculated in depth (Agarplate Rogosa SL (Difco).^[39]^ Brucella Agar plates will be incubated in anaerobic chamber (PLAS by LABS, LANSING, MICH., USA) at 37°C for 7 days. The plates of MitisSalivarius Agar and MitisSalivarius Bacitracin will be incubated in 10% CO2 (ShelLab CO2 greenhouse, mod. 2123, Oregon) at 37°C for 48 hours. Plates containing Rogosa Agar will be incubated in 10% CO2 at 37°C for 72 hours.^[39]^ After the incubation, the characteristic colonies will be counted in each plate, observed using a stereoscopic microscope with 10-fold increase, in the dilution that presented between 30 and 300 colonies per plate. All procedures will be performed in duplicate and the average counts will be calculated.

The results will be presented in CFU of SM and LB and in percentage of streptococci (% S/TM), streptococci mutans (% SM/TM), and lactobacilli (% LB/TM) in relation to total viable microorganisms. For SM, the proportion of total streptococci (% SM/S)^[15]^ will also be calculated. Immediately after removal of the carious tissue, the remaining dentin will be collected using the Meyhoefer auricular No. 17 curette and the same procedures described above will be adopted.

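### The plated dilutions leave lactobacilli at 3,000–30,000 CFU/mL, total microorganisms below 3×10^6 and streptococci below 3×10^5 without a countable plate

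*Protocol article*

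**What the plan says.** All of this stands in section 3.1.13 (Microbiological evaluation) of the protocol article. A dilution series from 10^1 to 10^6 is prepared, and four groups of organisms are plated from it:

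- Total viable microorganisms (TM): "Aliquots of dilutions 10^4^, 10^5^, and 10^6^ will be seeded on the surface of Brucella Agar".
- Total streptococci (S): "Aliquots of dilutions 10^3^ and 10^4^ will be seeded in MitisSalivarius agar medium".
- Streptococci mutans (SM): "Biofilm aliquots without dilution and at dilutions 10^1^ and 10^2^ will be seeded".
- Lactobacilli (LB): aliquots of 100 µL "without dilution and in the dilution 10^2^ will be inoculated in depth".

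For the surface-seeded media, "100 μL aliquots of each dilution will be seeded on the agar surface". Colonies are counted "in the dilution that presented between 30 and 300 colonies per plate", in duplicate, and the duplicates are averaged. The dentin remaining after removal goes through the same procedure, hence the same dilutions and the same counting range.

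The reporting sentence begins "The results will be presented in CFU of SM and LB and in percentage of streptococci (% S/TM" and adds %SM/TM and %LB/TM. %SM/S is calculated as well. TM therefore enters the presented results only as a denominator.

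**The concern.** A 30-to-300 window spans one factor of ten, so neighbouring tenfold dilutions give a continuous measuring range. The LB scheme skips 10^1, which opens a hole in the middle of its range. The TM and S schemes start at high dilutions and keep them for the post-treatment sample, the one in which a successful decontamination should show.

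At stake are LB CFU, the three percentages with TM as denominator, and %SM/S, whose denominator is S. CFU is also the variable named in the sample size paragraph (3.1.8), and decontamination is part of hypothesis H1 (3.1.2). If a tooth's TM or S count is lost because the bacteria were reduced, the loss is related to the effect under comparison.

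**Working it through.** **Inputs (all from 3.1.13):** plated volume 0.1 mL; countable range 30 to 300 colonies; dilutions as listed above; transport volume 3.8 mL. The article states no detection limit, so there is no figure of its own to reproduce first.

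**Formula:** CFU/mL = colonies ÷ 0.1 mL × dilution factor.

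| Organism | Dilutions plated | Countable CFU/mL | Consequence |
|---|---|---|---|
| LB | 10^0, 10^2 | 300–3,000 and 30,000–300,000 | gap 3,000–30,000 |
| SM | 10^0, 10^1, 10^2 | 300–300,000 | no gap |
| S | 10^3, 10^4 | 3×10^5–3×10^7 | floor 3×10^5 |
| TM | 10^4, 10^5, 10^6 | 3×10^6–3×10^9 | floor 3×10^6 |

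For TM the floor is 30 ÷ 0.1 × 10^4 = 3×10^6 CFU/mL, or 3×10^6 × 3.8 = 1.14×10^7 CFU per tube.

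**Inside the LB gap.** At a true 10,000 CFU/mL the undiluted plate expects 10,000 × 0.1 = 1,000 colonies and the 10^2 plate expects 10. Both lie outside 30–300.

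**Counting error.** The sum of duplicate plates was taken as Poisson with mean 2 × c × 0.1 ÷ 10^d, where c is the true CFU/mL and 10^d the dilution. A dilution is countable if that sum is 60 to 600. Failure probabilities were multiplied over the dilutions.

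- LB at 10,000 CFU/mL: chance of no countable plate 1.00 as planned, 0.00 if 10^1 is added.
- TM at 10^6 CFU/mL: 1.00 as planned, 0.00 if 10^2 and 10^3 are added.
- Only values at a limit are uncertain: LB at exactly 3,000 CFU/mL gives 0.489 as planned and 0.236 with 10^1 added.

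**Cap on two percentages.** The highest countable LB or SM is 3×10^5 and the lowest countable TM is 3×10^6. With both counts in range, %LB/TM and %SM/TM are at most 3×10^5 ÷ 3×10^6 = 10%.

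**Largest measurable TM reduction.** This is log10(baseline ÷ 3×10^6). From a baseline of 3×10^7 CFU/mL it is 1 log10.

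**Share of teeth affected (assumed levels).** The readable text gives no expected CFU level before or after treatment. The figures below assume normal log10 counts with SD 0.5 or 1.

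| Assumed mean log10 TM after treatment | Below floor, SD 0.5 | Below floor, SD 1 |
|---|---|---|
| 8 | 0.1% | 6.4% |
| 7 | 14.8% | 30.1% |
| 6 | 83.0% | 68.3% |
| 5 | 99.8% | 93.0% |

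For LB with assumed means of 3 to 5 log10 CFU/mL, between about 15% and 68% of samples fall in the gap.

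**The case against.** **The best-treated teeth do not lose their counts across the board.** A reader might infer that they do. The documents do not support that. The LB gap lies mid-range: a tooth brought down to 300–3,000 CFU/mL is countable again, and a tooth can sit in the gap at baseline. SM CFU is continuous from 300 to 300,000 and is spared by both faults. %SM/S does not use TM, although it does depend on the S floor. TM CFU is not itself a presented result. Only the TM and S floors can tie loss to low counts, and they apply in both arms and at both time points.

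**Missing data are not stated.** The article says which dilution is counted. It does not say that a sample with no plate in range is discarded. Such plates are not empty: at TM 10^6 CFU/mL the 10^4 plate expects 10 colonies, in duplicate. With an assumed mean of 7 and SD 1, about 30% of samples are below the floor, but only about 2% expect less than one colony on that plate; at mean 6 the figures are 68% and about 16%. The handling of out-of-range plates may stand in the full protocol or the SAP. This is fair, and it is why the claim is limited to results that may be unavailable or poorly estimated. But the dilutions are fixed in the text, and no later analysis rule can recover plates that were never poured.

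**No bias direction is shown.** A reader might infer a bias against the photodynamic arm. That would need a difference between arms near the floor, and the article gives no figure for one.

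**The conversion might differ.** If the dilution labels already included the 0.1 mL, every limit would be ten times lower (TM floor 300,000). The text gives 100 µL of each dilution, which speaks against this. The tenfold LB gap and the 10% cap would remain either way.

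**Microbiology is not primary.** The primary outcome is VAS sensitivity (3.1.12). This stands and limits the weight of the point.

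**Conclusion.** The point holds in a limited form. The LB gap (3,000–30,000 CFU/mL), the TM floor (3×10^6), the S floor (3×10^5) and the 10% cap on %LB/TM and %SM/TM follow exactly from the stated volume, dilutions and counting range, with no outside assumption. LB CFU, the three TM-based percentages and %SM/S may therefore be unavailable or poorly estimated for some teeth, before or after treatment. For TM and S the loss can depend on the reduction being compared.

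How many teeth are affected cannot be estimated from the documents. For TM the share runs from 0.1% to 99.8% over assumed post-treatment means of 8 to 5 log10 CFU/mL with SD 0.5 to 1. Neither a loss confined to the best-treated teeth nor a bias in a given direction is established. This is a worthwhile and inexpensive improvement to non-primary outcomes.

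**What to change.** - Plate LB also at 10^1 in both samples. The range becomes continuous from 300 to 300,000 CFU/mL.
- In the post-treatment sample, plate TM also at 10^2 and 10^3 (floor 30 ÷ 0.1 × 10^2 = 30,000 CFU/mL) and S also at 10^1 and 10^2 (floor 30 ÷ 0.1 × 10 = 3,000 CFU/mL).
- State that a count below the lowest plate is left-censored at that limit and not treated as missing.

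The lower TM floor also removes the 10% cap in the post-treatment sample, since 3×10^5 ÷ 30,000 exceeds 1. At baseline the cap stays unless the extra TM plates are poured there too.

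**Cost:** all tubes are already in the 10^1 to 10^6 series, so no extra sample or visit is needed. Taking duplicate to mean two plates per dilution, the addition per tooth is LB 1 × 2 × 2 samples = 4, TM 2 × 2 = 4 and S 2 × 2 = 4, or 12 plates. The present scheme uses (3 + 2 + 3 + 2) dilutions × 2 plates × 2 samples = 40.

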#### Interventions

3.1.7

##### Group 1

3.1.7.1

1.Initial interproximal radiography;2.Relative insulation (lip retractor, cotton roller, and saliva sucker);3.Taking the VAS scale for pain as responded by the volunteer;4.Microbiological outlet with an otoscopic curette to standardize the volume of carious tissue;5.Application—(PapacarieMblue), leave action for 20 seconds and remove the softened carious tissue just around the sidewalls of the cavity with blunt dentin spoons. Wait another 3 minutes to act on the blue dye present in the gel composition;6.Radiate with the low power laser (single point), following the parameters described in item 3.1.10;7.Clean with cotton ball and water;8.Second microbiological outlet with curette of remaining dentin tissue;9.Clinical evaluation by inspection of remaining dentin texture with rounded probe exploratory probe;10.Clean with cotton ball and water again;11.Sealing the cavity with glass ionomer cement (Riva Self Cure/HV - SDI);12.Taking VAS for Pain Responded by Volunteer;13.Preservation;14.Radiographic control 6 and 12 months.

##### Group 2

3.1.7.2

1.Initial interproximal radiography;2.Relative insulation (lip retractor, cotton roller, and saliva sucker);3.Microbiological outlet with an otoscopic curette to standardize the volume of carious tissue;4.Removal of the softened dentin dentine around the lateral walls of the cavity with sharp dentine curettes # 17;5.Second microbiological outlet with dentin curette;6.Clinical evaluation by inspecting the texture of the remaining dentin with exploratory catheter;7.Clean with cotton ball and water;8.Sealing the cavity with glass ionomer cement (Riva Self Cure/HV - SDI);9.Preservation;10.Radiographic control 6 and 12 months.

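### Two differently numbered curettes are named for the before and after dentin samples, so the within-tooth change in absolute CFU is open to a sample-amount artefact of unknown size and direction

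*Protocol article*

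**What the plan says.** Section 3.1.13 (Microbiological evaluation) describes the first sample, taken before caries removal: "The removed tissue will be standardized using a No. 2 Meyhoefer curette". The tissue is then "deposited in a test tube containing 3.8 mL of Transport Medium-Phosphate Buffered Saline". For the second sample, taken straight after removal, "the remaining dentin will be collected using the Meyhoefer auricular No. 17 curette", and "the same procedures described above will be adopted". The section reports CFU of SM and LB. It also reports total streptococci (S), SM and LB as percentages of total viable microorganisms (TM), and SM as a percentage of S.

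Section 3.1.7 (Interventions) gives the first sampling step in the same words for both groups: "Microbiological outlet with an otoscopic curette to standardize the volume of carious tissue". The second sampling step carries no curette number and no volume standard. For Group 1 it reads "Second microbiological outlet with curette of remaining dentin tissue"; for Group 2 it reads "Second microbiological outlet with dentin curette". The number 17 appears once more in 3.1.7, where the Group 2 excavation is done "around the lateral walls of the cavity with sharp dentine curettes # 17".

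Section 3.1.8 (Sample size) bases the calculation on CFU, treated as paired samples, with a 5% level and 80% power, and reaches a minimum of 16 teeth per group. Section 3.1.9 plans 24 per group. Section 3.1.12 labels dentin sensitivity on the VAS as the primary outcome.

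**The concern.** A before-after count is interpretable only if the same amount of material is sampled each time, or if the count is divided by that amount. Here the curette cup is the device chosen to hold the amount constant, yet a differently numbered cup is named for the second sample. The suspension volume is fixed and no weighing is mentioned. Any difference in cup volume would therefore pass straight into the absolute CFU.

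At stake is the within-tooth change in CFU of SM and LB. Decontamination is part of H1 in section 3.1.2. A bacterial reduction could be exaggerated, masked or produced by the instruments alone. The repeated number 17 adds a practical ambiguity: an operator following the text could take the second sample with the size used to excavate Group 2.

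**Working it through.** **The plan's own figure.** The minimum of 16 teeth per group cannot be reproduced, because the expected difference and its SD are not legible in the available text. Back-solving the paired formula n = ((1.96 + 0.84) × SD / difference)² at n = 16 gives difference/SD = 2.80/4 = 0.70. The point below does not change that number.

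**Effect of a volume ratio.** Let r be the volume of the second cup divided by that of the first. Assume that each cup is filled to capacity and that recovered CFU are proportional to the tissue sampled. Then:

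observed log10 change = true log10 change + log10(r)

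No value of r is given, so a range is shown.

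| r | Shift (log10) | Apparent change with no kill | A true 90% kill reads as |
|---|---|---|---|
| 0.25 | −0.60 | −75% | 97.5% |
| 0.5 | −0.30 | −50% | 95% |
| 0.8 | −0.10 | −20% | 92% |
| 1 | 0 | 0 | 90% |
| 1.25 | +0.10 | +25% | 87.5% |
| 2 | +0.30 | +100% | 80% |
| 4 | +0.60 | +300% | 60% |

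The third column is r − 1. The fourth is 1 − 0.1 × r.

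**What is not affected.**
- Percentages: (r × SM)/(r × TM) = SM/TM. The same cancellation holds for % S/TM, % LB/TM and % SM/S.
- Between-arm log contrast: (true change in arm 1 + log10 r) − (true change in arm 2 + log10 r) has no r left in it. For example, true kills of 99% and 90% differ by −1.0 log10 at r = 0.5, 1 and 2 alike.
- This cancellation needs the same r in both arms. With different ratios, log10(r₁/r₂) remains.
- A difference in raw counts is multiplied by r. From a baseline of 100,000 CFU and the same two kills, the after-treatment difference is 4,500, 9,000 or 18,000 at r = 0.5, 1 or 2.

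**Conditional false-positive rates.** These depend on an assumed r, an assumed SD of the paired log10 change, and a two-sided 5% paired t-test (noncentral t, noncentrality = log10(r) × √n / SD). With SD 1.0 and no true kill:

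| Ratio, either direction | n = 24 | n = 16 |
|---|---|---|
| 1 | 5% | 5% |
| 1.25 | 7% | 7% |
| 1.5 | 13% | 10% |
| 2 | 29% | 20% |
| 3 | 61% | 43% |
| 4 | 81% | 62% |

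At a ratio of 2 and n = 24, moving the assumed SD from 0.5 to 1.5 moves the rate from 81% to 16%.

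**The case against.** The strongest reply is that different numbers do not prove different volumes. The article does not say whether Nos. 2 and 17 differ in capacity or only in shape. This stands: a reader might infer that the CFU change is biased, but the text shows only that nothing prevents it.

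A reader might also take the within-arm fall in CFU as the trial's main decontamination result. The documents do not say so. The specific objective compares aPDT with ART, the primary outcome is VAS sensitivity, and the wording about fewer viable bacteria sits inside H0. Even with identical curettes, a within-arm fall would not isolate bacterial kill, because softened tissue is removed between the two samples. The between-arm log contrast is the more interpretable one, and a constant r cancels there. Section 3.1.13 names the No. 17 without separating the groups. The looser wording of the two step lists does not show that the arms use different instruments, though it does not secure that they use the same one.

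The false-positive rates invite a third over-reading. Section 3.1.17 names ANOVA and Kruskal–Wallis for CFU, not a paired t-test. At a ratio of 1.25 with SD 1.0, the rate is close to nominal.

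Two further replies do not remove the point. The statement that the same procedures apply to the second sample could be read to cover standardised collection, but the same sentence names another curette. The 17 may also be a slip carried over from the excavation step. If so, the text still needs correcting, because two instruments are expressly named for one before-after pair. Missing weighing would not be a finding on its own in a condensed article. It matters here only because it leaves the curette as the sole stated control.

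**Conclusion.** The inconsistency is real: section 3.1.13 names a No. 2 and then a No. 17 curette, and section 3.1.7 attaches the volume standard to the first sample only. As written, the within-tooth change in absolute CFU of SM and LB is shifted by log10 of the cup-volume ratio, which is zero if the volumes are equal and 0.30 log10 if they differ twofold. Size and direction are unknown, so this is a possible artefact and not a demonstrated bias. The percentage outcomes are safe. The between-arm log contrast is safe provided both arms use the same pair of instruments.

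The point does not touch the VAS primary outcome, but it concerns the variable on which the sample size rests. It should be corrected because the correction costs so little. Any false-positive rate quoted with it must be labelled as conditional on an assumed ratio, an assumed SD and a paired test that the plan does not name.

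**What to change.** Reconcile sections 3.1.7 and 3.1.13. Name one sampling curette size, filled level, for both time points and both arms. Specify a fresh sterile instrument for each sample, separate from the one used for excavation. Put the volume-standardising wording on the second sampling step in both groups as well.

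If two sizes must be kept, either weigh the sample and report CFU per mg, or rest the decontamination conclusion on the between-arm contrast of log10 change and on the percentage outcomes, with the same pair of curettes in both arms.

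The cost is a wording change and a second sterile curette per tooth. Weighing, if chosen, adds a short laboratory step per tube. The planned number of teeth does not change.

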#### Radiographic evaluation

3.1.14

Interproximal radiographs will be performed initially, aiming at assessing the presence of caries on the proximal surface (adjacent surfaces), radiolucency compatible with carious lesion in dentin, deep caries and to rule out the possibility of pulp involvement. Hereafter, the controls will be in 6 and 12, to analyze the optical density and visual clinical interpretation of the remaining dentin, even as the evaluation with the radiographic subtraction technique.^[40]^ All images will be made with KODAK Double Films. To better understand the application of the radiographic subtraction technique, the 4 radiographs will be compared and must be taken with the minimum geometrical distortion, which is achieved by individualizing prefabricated radiographic film positioners by means of occlusal records with self-curing acrylic resin, specific for each patient. These should be stored for subsequent radiographic shots.

The radiographic processing should be standardized, such as the time of radiographic exposure, kilovoltage and mili-amperage of the apparatus, and type of film, in order to obtain density and contrast as “identical” as possible between the images.^[40–42]^ The standardization of radiographic processing will be used and the same time of revealing, intermediate washing, fixation, and final washing, in all periods, should be the same. The chemicals used will be Kodak. The images obtained radiographically in the different intervals will be scanned for analysis of the density difference between them. To do so, the program Imagelab 2.3^[41]^ will be used. Thus, it is expected that the density of the remaining dentin will follow the variations in optical density, so they will be evaluated in the time intervals between 6 and 12 months after therapeutic application in all groups. The objective will be to quantitatively determine the gray tones of the affected dentin region just below the restoration in glass ionomer and compare the density of the remaining dentin in both groups.^[41–44]^

#### Evaluation of time required for procedure

3.1.15

The necessary time for each procedure will be measured using a stop watch (Kenko, Hong Kong) in minutes and seconds from the onset of treatment until complete curettage of soft dentine and restoration. Time will be recorded on a specific chart for analysis.

#### Clinical evaluation

3.1.16

The criteria used for clinical evaluation are the retention of the material in the cavity and the presence of secondary caries. The evaluation scores will be evaluated based on the results of studies by other authors (Frencken et al).^[11]^ Digital photographs of the restorations will also be performed to complement the elements of clinical and radiographic information. The visual demonstration can contribute to the necessary clarifications and make the discussion and documentation of the cases in this study more efficient. Therefore, digital photographs (Canon Sx500 IS camera), of all the teeth, will be performed in the 2 groups, before and after the interventions. The teeth will be classified as follows

0 = present, without defect.

1. = present, small defects in the margin less than 0.5 mm deep, no need for repair.

2. = present, small defects in the margin of 0.5 to 1 mm depth, needs repair.

3. = present, gross defects in the margin of 1 mm or more in depth, needs repair.

4. = absent, restoration almost / completely lost, needs treatment.

5. = absent, other treatment was performed for any other reason.

6. = tooth missing due to any reason.

7. = present, surface wear less than 0.5 mm, no need for replacement.

8. = present, surface wear greater than 0.5 mm, need replacement.

9. = impossible to diagnose.

